## **Abstract**

### **Justification:**

Depression is one of the most common and serious illnesses worldwide and has a significant negative impact on patients' quality of life and ability to work. Patients with depression exhibit changes in the gut microbiome and its metabolites, which in turn influence the gut-brain axis as a bidirectional communication system. A key component of this axis is the vagus nerve, which transmits information from the internal organs in the periphery to the central nervous system. Studies have shown that the function of the vagus nerve is impaired in patients with depression. At the same time, depressed patients often have a pro-inflammatory status, which is linked to the function of the vagus nerve in influencing the immune response. Animal models have shown that vagal afferents transmit information from intestinal bacteria directly to the central nervous system and can thus induce both anxious and depressive behaviour. Stimulation of the vagus nerve (which is currently used clinically as an invasive procedure for treatment-resistant depression) has been shown to improve depression and alleviate (neuro)inflammation. A pilot study from our working group has shown that the diversity of the gut microbiome in women correlates with the function of the vagus nerve ([name]/Oberascher et al., 2020, in prep).

**Relevance:** To date, no research has been conducted into whether and to what extent probiotics can influence the function of the vagus nerve. This new mechanism could be used to specifically alter the function of the vagus nerve with probiotics and provide a rationale for add-on therapy with probiotics ("psychobiotics").

**Design:** This monocentric study will investigate the effect of a multi-strain probiotic on vagus nerve function in 40 depressed patients and 40 healthy control subjects in a placebo-controlled setting. The study participants will receive either a probiotic or a placebo for 3 months, and the function of the vagus nerve will be determined at 4 time points using a portable ECG, which will be worn for 24 hours. In addition, inflammation markers (hs-CRP, IL-6) and the gut microbiome were determined using 16S sequencing. This is the first study worldwide to investigate the effects of a multistrain probiotic on the vagus nerve in depressed patients compared to healthy control subjects. The results of this study could contribute to a better understanding of the basis of probiotic effects on mental processes.

## 1. Scientific background

According to the WHO, depression is one of the most common diseases, and the associated health and socio-economic problems place a heavy burden on both those affected and society as a whole. Despite intensive efforts to improve the treatment of depression, psychopharmacological therapy still only leads to complete remission in one third of patients (1). Combination therapies of antidepressants and psychotherapy are used to treat depression, with approximately 50% of patients discontinuing antidepressant treatment prematurely due to side effects (2). This underscores the need for further research into the mechanisms underlying this disease in order to develop more tolerable and effective treatment options.

Depressed patients predominantly show profound changes in their gut microbiota composition, which in turn affects the intestinal barrier and inflammatory status. The largest study currently available on the gut microbiome and depressive symptoms has shown that while the butyrate-producing *Faecalibacterium* and *Coprococcus* bacteria are associated with a higher quality of life, *Dialister* and *Coprococcus* spp. are negatively correlated with depression (3). A meta-analysis of intervention studies with probiotics showed a significant improvement in depressive mood compared to healthy controls (SMD = -1.62, 95% CI = -2.73 to -0.51,  $p < 0.01$ ) (4). However, the exact mechanisms responsible for improving depression are still the subject of research.

In our pilot study, we were able to show that the diversity of the gut microbiota correlates with the function of the vagus nerve, the tenth cranial nerve and main player in the microbiota-gut-brain axis (Oberascher/[name] et al., 2020, in prep.). This points to an interaction between the gut microbiome, inflammation and the function of the vagus nerve. The afferents of the vagus nerve are polymodal and therefore respond to mechanical, chemical and hormonal signals (5, 6). Stress and depression influence its function. Depressed patients show reduced vagus function and reduced heart rate variability, which is a biomarker of the vagus nerve (7, 8). In addition, there is increasing

evidence that the nervous system controls inflammatory processes and dampens the immune response via the vagus nerve and oxytocin (9), with heart rate variability (HRV) being particularly associated with blood levels of C-reactive protein (CRP) (10) and interleukin-6 (IL-6). The inflammatory hypothesis of depression describes how inflammatory processes in the brain lead to depressed mood and anxiety (11, 12). Older reports on vagotomy in humans, which was previously performed to treat peptic ulcer disease, show a positive correlation with the occurrence of psychiatric disorders (13, 14). and underscore the important role of the vagus nerve in the pathogenesis of depression. In addition, experimental procedures for electrical vagus nerve stimulation are now being used to treat treatment-resistant depression (15).

Our previous studies suggest that changes in the gut microbiome are associated with psychiatric disorders (16, 17) and that probiotic interventions affect the inflammatory status (IL-6) in depressed patients by reducing interleukin-6 gene expression (18) and that gut microbiota diversity correlates with vagus nerve function as measured via HRV (logarithm of respiratory sinus arrhythmia (logRSA), HR, PRQ) (Oberascher/[name] et al., 2021, in prep.). Probiotics alter the composition of gut bacteria and their metabolites (18) and could thus influence vagal afferents that transmit signals to the hypothalamus via the nucleus tractus solitarius (NTS). In animal models, bacteria such as *Escherichia coli* were able to trigger vagal afferent neurons and act on the CNS (19). Gut bacteria such as *Bifidobacterium longum* use the vagus nerve to transmit signals from the gastrointestinal tract to the brain (20, 21).

Heart rate variability (HRV) measures cardiac autonomic regulation and describes the degree of fluctuation in heartbeats (R-R intervals) that can be derived from an electrocardiogram. These intervals are not constant and vary with each heartbeat. Basically, a higher HRV means better vagus nerve function and better health (10). Reduced vagus nerve function is associated with a reduction in HRV and a monotonous regularity of heart rate (22). A meta-analysis of HRV in depressed patients showed that they had reduced HRV indices compared to healthy control subjects and that depression correlated negatively with HRV (23). HRV is associated with inflammatory markers (CRP and IL-6). For example, Jarczok et al. showed that vagus nerve function could predict CRP levels (10, 23).

## Data available to date

Studies conducted by our working group indicate changes in the gut microbiome in mental illnesses such as depression, bipolar disorder and anorexia nervosa (16, 17, 24). In addition, we were able to show that the administration of a multi-species probiotic significantly influences interleukin-6 gene expression in depressed patients compared to placebo (18). To the best of our knowledge, however, there are only a few studies that have investigated the influence of probiotics on vagus nerve function, and no psychiatric studies on this topic, although studies in mice have shown promising effects of probiotics on vagus nerve function (25). There is also an interventional study with a multispecies probiotic in women with hypertension. Romao da Silva et al. observed changes in HRV after an 8-week intervention with *Lactobacillus paracasei* LPC-37, *Lactobacillus rhamnosus* HN001, *Lactobacillus acidophilus* NCFM, and *Bifidobacterium lactis* HN019 ( $10^9$ CFUs for each strain), indicating an improvement in autonomic regulation. This mechanism has not yet been researched in relation to mental illness.

## 2. Aims of the study

The aim of this study is to investigate the effects of probiotics on vagus nerve function in patients with depression (mild, moderate and severe depressive episodes, or recurrent depressive disorder). Furthermore, the 3-month administration of a multi-species probiotic will be used to evaluate a possible improvement in depressive symptoms. The change should be measurable not only clinically, but also on the basis of various markers (i.e. in the areas of inflammation, tryptophan metabolism and the microbiome). For this pilot study, we will invite patients who are being treated for depression as inpatients at the University Clinic for Psychiatry and Psychotherapeutic Medicine.

The clinical examinations will be carried out by the above-mentioned study team (i.e. using MedUni's own funds), but a study nurse/study assistant will be required to coordinate the visits for the duration of the study. The biological parameters will be evaluated by cooperation research partners (Graz). A

funding application has been sent to the City of Graz. Part of the costs will also be financed by Allergosan. The probiotics and placebo will be provided by Allergosan.

### 3. Study procedure

#### Study design

This study is being conducted at the University Clinic for Psychiatry and Psychotherapeutic Medicine as a monocentric, randomised study. Randomisation is carried out by Allergosan (block randomisation). Patients at the University Clinic for Psychiatry who meet the inclusion criteria are invited to participate. Healthy control subjects will be recruited by Probando (probando.io) as well as via social media and notices on bulletin boards. A total of four **study visits** will take place. During the clinical visits, blood samples will be taken, psychological and cognitive tests will be conducted, and a clinical interview will be held to record any possible side effects and symptoms. The psychiatric diagnosis is made at the start of the study by a psychiatrist using the M.I.N.I. (Mini International Neuropsychiatric Interview [24]).

#### Study visits

[figure not shown]

Figure 1. Study visits

#### Visit 1 Procedure:

- Blood sampling

- Stool
- Heart rate variability (device is attached and worn for 24 hours)
- Each patient receives a month's supply of probiotics (approx. 30 capsules in total) labelled with their assigned number. The first dose is prepared and consumed together with the study doctor or study psychologist.
- Anthropometry
- Questionnaires

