#### **Visit 2 Procedure:**

- Patient compliance is measured by having patients bring their daily probiotic rations back to the visit (i.e. after 1 month) and checking and noting the number of doses taken or not taken.
- Blood
- Stool (can be brought along, max. 1 day old and stored in a cool place) including stool log
- Anthropometry
- Questionnaires
- Heart rate variability (device is attached and worn for 24 hours)
- Each patient receives a ration of probiotics labelled with the respective assigned number for 2 additional months (a total of approx. 60 units).

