## 5. Methods

### 5.1 Intervention with multispecies probiotic

The multistrain probiotic and placebo used are provided by the Allergosan Institute. This is a commercially available dietary supplement called OMNi-BiOTiC® -SR, which contains 9 bacterial strains (*Bifidobacterium bifidum* W23, *Bifidobacterium lactis* W51, *Bifidobacterium lactis* W52, *Lactobacillus acidophilus* W22, *Lactobacillus casei* W56, *Lactobacillus paracasei* W20, *Lactobacillus plantarum* W62, *Lactobacillus salivarius* W24, *Lactococcus lactis* W19) with at least 7.5 trillion microorganisms per serving (=3g).

The placebo preparation will have the same colour, consistency and taste as the probiotic product. The matrix of the product contains corn starch, maltodextrin, inulin, potassium chloride, magnesium sulphate, fructooligosaccharides, amylases and manganese sulphate. Patients and healthy controls receive OMNi-Biotic SR after it has been dissolved in water and the activation time of 10 minutes has been observed. For inpatients, the study preparation is prepared daily at 7:00 a.m. by study staff and given to inpatients before breakfast and in the evening every day until discharge. After discharge, patients continue to take the preparation twice daily at home on their own. The entire study team is blinded.

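### About one unit per day is dispensed but patients are to take the product twice daily; unit, form and frequency are not reconciled, and the listed 3-month procedures include no return count

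*Protocol*

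**What the plan says.** **Dispensing.** Section 3, Visit 1 Procedure, gives each patient one month's "supply of probiotics (approx. 30 capsules in total) labelled with their assigned number". Visit 2 Procedure gives a further ration "labelled with the respective assigned number for 2 additional months (a total of approx. 60 units").

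**Intake.** Section 5.1 says the preparation is "given to inpatients before breakfast and in the evening every day until discharge". It continues: "After discharge, patients continue to take the preparation twice daily at home on their own". Healthy controls are said to receive the dissolved product, but no frequency is stated for them.

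**Form.** Section 5.1 defines the content by "microorganisms per serving (=3g"), dissolved in water with a 10-minute activation time. Visit 1 calls the items capsules and Visit 2 calls them units.

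**Duration.** The Abstract states: "The study participants will receive either a probiotic or a placebo for 3 months".

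**Compliance.** At Visit 2, after one month, patients bring back their daily rations and staff record intake by "checking and noting the number of doses taken or not taken". The list for the 3-month follow-up appointment has blood, stool, anthropometry, questionnaires and heart rate variability, with no return or count of product.

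**The concern.** The number of units handed out and the described intake are both instructions that site staff act on, and on a plain reading they differ by a factor of two. Followed literally, a patient could run out of product part-way through each dispensing period, or could take fewer doses per day than section 5.1 describes. Different patients could resolve the conflict in different ways, so exposure would vary within the probiotic arm for reasons unrelated to the trial question.

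The record of exposure is affected too. A count of doses taken can be interpreted only against the number that should have been taken, and the protocol allows two such numbers. This matters more because the per-protocol analysis is the primary one (section 6.1) and serious violations of the project plan remove a case from it. For months 2 and 3 the listed procedures record no intake at all.

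**Working it through.** **Inputs.**
- Units dispensed: about 30 at Visit 1 for one month; about 60 at Visit 2 for two more months (section 3).
- Intake for patients: 2 per day, in hospital and after discharge (section 5.1).
- Treatment period: 3 months (Abstract).
- Assumed calendar lengths, since the protocol gives only months: 28, 30 or 31 days for month 1; 56, 60 or 62 days for months 2-3; 84, 90 or 92 days in total.
- Assumption for step 2: one unit is one dose. The protocol does not define a unit.

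**Step 1: reproduce the stated supply.** Units needed = units per day x days. At one unit per day:
- Month 1: 1 x 30 = 30 (stated: 30)
- Months 2-3: 1 x 60 = 60 (stated: 60)
- Total: 1 x 90 = 90 (stated: 30 + 60 = 90)

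The stated supply corresponds to one unit per day.

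**Step 2: the same formula at twice daily, one unit per dose.**

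| Period | Need (range) | Stated | Stated / need (range) | Days the stock lasts |
|---|---|---|---|---|
| Month 1 | 2 x 30 = 60 (56 to 62) | 30 | 0.50 (0.48 to 0.54) | 30 / 2 = 15 |
| Months 2-3 | 2 x 60 = 120 (112 to 124) | 60 | 0.50 (0.48 to 0.54) | 60 / 2 = 30 |
| Total | 2 x 90 = 180 (168 to 184) | 90 | 0.50 (0.49 to 0.54) | 90 / 2 = 45 |

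No plausible month length brings the two together, and a factor of two is too large to be covered by the word for approximate in the dispensing lines.

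**Step 3: the alternative meaning of a unit.** If one unit is a daily ration holding both doses, the need is one unit per day and step 1 applies: 30 and 60 units fit. The Visit 2 reference to daily rations is compatible with this. However, no passage says that a unit holds two doses, and section 5.1 does not link its 3 g serving to a unit.

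**Step 4: consequence for the Visit 2 count.** Suppose a patient has used all 30 units at day 30. Against 30 expected units, that is 30/30 = 100%. Against 60 doses at one unit per dose, it is 30/60 = 50%. The protocol states no expected count, so the same observation supports either figure.

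**Step 5: coverage of the count.** The count at Visit 2 covers month 1, which contains the 4-week period of the primary hypothesis (section 3.2). The 60 units for months 2-3, two of the three treatment months, have no count in the listed procedures. Those months bear mainly on secondary hypothesis 2, which concerns the state after 3 months of intervention.

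**The case against.** The strongest reply is that the factor of two is not a fact of the document. It depends on one unit being one dose, and under the daily-ration reading there is no shortage. This stands as a limit on the size of the problem. It does not remove the problem, because the reader has to supply a definition that the protocol lacks.

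Several stronger readings are tempting, and the document does not support them:

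- **That all participants would run out or be under-exposed.** Twice daily is stated for patients only, so nothing can be computed for the 40 healthy controls. For inpatients, staff prepare the product, and whether they draw on the dispensed units is not stated. With separate ward stock the 30 units would last longer, although they are still called a month's supply.
- **That the 3-month outcome comes from an unexposed period.** Even at one unit per dose, stock would last 30 of the 60 days in months 2-3. At worst the second part of that period is uncovered.
- **That the expected count is wrong by a factor of two.** The protocol sets no expected count, denominator or compliance threshold, so there is no such figure to be wrong. The defect is ambiguity.
- **That the per-protocol set cannot identify non-takers.** Month 1 has a count, and it covers the 4-week primary period. The gap in the listed procedures is months 2-3.
- **That product is counted at Visit 2 and nowhere else.** Four visits are announced and procedures are listed for three; the visit figure is not available here. The statement can be made only about the listed procedures.

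It is also fair to say that capsules may be a slip of one word, since Visit 1 itself has the first dose prepared before it is consumed, which fits a dissolved product. It still needs correcting, because the form determines what a countable unit is.

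**Conclusion.** The dispensing lines of section 3 and the intake described for patients in section 5.1 do not agree on a plain reading, and nothing in the protocol reconciles them. If one unit is one dose, the stated supply of about 90 units meets about half of the roughly 180 (168 to 184) needed at twice daily; if one unit is a daily ration, the figures agree. The inconsistency itself is certain, while its effect on actual exposure is conditional on the meaning of a unit, applies to patients only, and depends on where inpatient doses come from.

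The compliance consequence is narrower. The Visit 2 count exists and covers the primary 4-week period, but it lacks an unambiguous number to be judged against. Intake in months 2-3 is not recorded in the listed procedures, which weakens mainly the 3-month secondary hypothesis.

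This should be corrected before the protocol is followed as written, because exposure that was lost or not recorded cannot be recovered at analysis. Which frequency or number is right is for the sponsor to settle.

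**What to change.** 1. The sponsor reconciles Visit 1 Procedure, Visit 2 Procedure and section 5.1 on four items: what a unit is and how it relates to a dose, the product form, the intake frequency (for patients and for healthy controls), and the number dispensed at each visit. The text should also say whether inpatient doses are drawn from the dispensed units.
2. From the reconciled text, state the expected number of units used by each visit, so that the count has a fixed reference.
3. Add the return and count of units from months 2-3 to the procedures of the existing 3-month appointment.

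The cost is a protocol correction, one extra count at a visit that already takes place and, if the dispensed number proves to be the figure that changes, an adjusted product supply.

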#### **Visit 2 Procedure:**

- Patient compliance is measured by having patients bring their daily probiotic rations back to the visit (i.e. after 1 month) and checking and noting the number of doses taken or not taken.
- Blood
- Stool (can be brought along, max. 1 day old and stored in a cool place) including stool log
- Anthropometry
- Questionnaires
- Heart rate variability (device is attached and worn for 24 hours)
- Each patient receives a ration of probiotics labelled with the respective assigned number for 2 additional months (a total of approx. 60 units).

#### **Follow-up appointment (i.e. after 3 months):**

- Blood sample
- Stool (can be brought along, max. 1 day old and stored in a cool place) including stool log
- Anthropometry
- Questionnaires
- Heart rate variability (device is attached and worn for 24 hours)

### **3.1 Inclusion and exclusion criteria**

**Inclusion criteria** for this study are: informed consent, diagnosis of depression according to ICD-10, age between 18 and 65 years.

**Exclusion criteria** are: suicidal tendencies, lack of consent or capacity to consent, known cardiovascular disease, pregnancy, breastfeeding, pronounced dependence on alcohol or psychotropic substances (benzodiazepines, morphine), other severe mental or organic diseases (epilepsy, brain tumours, trauma, recent major surgery), tumour diseases, dementia (Mini Mental Score <20), severe autoimmune diseases or immunosuppression (lupus erythematosus, HIV, multiple sclerosis), antibiotic therapy in the last month, laxative abuse, acute

infections, diarrhoea, gastrointestinal surgery (except appendectomy). Participants should not have taken probiotics in the last 6 months. Furthermore, they should not consume any additional dietary supplements or probiotics during the study period. The additional intake of antibiotics or prebiotic supplements is also considered an exclusion criterion.

### **3.2 Questions and hypotheses**

The **hypotheses** of this study are as follows:

#### Primary hypotheses:

##### H(0):

A 4-week intake of a multi-species probiotic shows no significant increase in vagus function (measured by HRV, log RSA) and no significant decrease in inflammation parameters (IL-6, hsCRP) in subjects with depression and in healthy control subjects compared to placebo treatment.

##### H1:

A 4-week intake of a multi-species probiotic shows a significant increase in vagal function (measured by HRV, log RSA) and a significant decrease in inflammation parameters (IL-6, hsCRP) in subjects with depression and in healthy control subjects compared to placebo treatment.

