## 4. Target parameters

### 4.1 Primary endpoints

The target parameters for the main hypothesis are logRSA of HRV as a marker of vagus nerve function and the inflammation markers (hs-CRP, IL-6).

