## 6.1 Data analysis and evaluation

The data obtained will be analysed using IBM SPSS, version 27. A descriptive data description (mean, standard deviation, percentile rank) will be provided. Correlations between variables will be calculated using Pearson's correlation coefficient or Spearman's correlation coefficient, depending on the distribution. Error probabilities below  $p < 0.5$  are considered statistically significant. Microbiome analyses are performed in R (version 3.6) and Rstudio (version 1.2.1555) (R-doundation, Vienna, Austria), with visualisations using the ggplot2 library.

Both an intention-to-treat and a per-protocol analysis are performed.

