## 6.2 Considerations regarding the number of cases

This project is a pilot study. To the best of our knowledge, probiotic effects on vagus function in depressed patients have never been investigated before. A power analysis was performed using G\*Power 3.1.(29). In the F-tests category, the

"Repeated Measures ANOVA within-between interaction" was selected as the procedure. With a low effect size of 0.2, alpha 0.05 and 95% power, a total of 80 participants (20 participants per group) is required for 4 groups (healthy subjects: probiotic/placebo; depressed patients: probiotic/placebo).

[figure not shown]

Figure 3: Sample size calculation with G\*Power

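### H0 and H1 are opposite extremes over three unranked primary endpoints in two populations, so a mixed result has no defined verdict and the stated power fits neither success rule

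*Protocol*

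**What the plan says.** Protocol section 3.2 gives one pair of primary hypotheses. Under H(0), the probiotic "shows no significant increase in vagus function (measured by HRV, log RSA) and no significant decrease in inflammation parameters". Under H1, the expected result is "a significant increase in vagal function (measured by HRV, log RSA) and a significant decrease in inflammation parameters (IL-6, hsCRP) in subjects with depression". Both statements cover two populations: "in subjects with depression and in healthy control subjects compared to placebo treatment".

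Section 4.1 confirms that all three markers are primary and gives no order: "The target parameters for the main hypothesis are logRSA of HRV as a marker of vagus nerve function and the inflammation markers (hs-CRP, IL-6").

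Section 6.2 sizes the trial on a single test, the "Repeated Measures ANOVA within-between interaction" in G\*Power: "With a low effect size of 0.2, alpha 0.05 and 95% power, a total of 80 participants (20 participants per group) is required for 4" (the last figure being the number of study arms).

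Section 6.1 (data analysis) gives one general threshold below which results "are considered statistically significant". It is printed as 0.5, which conflicts with the 0.05 in section 6.2. That is a separate point, and 0.05 is used here. No section says whether one, some or all of the component results are needed for the primary hypothesis.

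**The concern.** A null and an alternative hypothesis should divide the possible truths between them. Here both are built with 'and'. H0 is that nothing improves and H1 is that everything improves, across three endpoints and two populations. Between them lie the most plausible outcomes: logRSA improves but IL-6 does not, or patients respond and healthy controls do not. In those cases H0 is contradicted and H1 is not supported.

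Two different success rules can be read from this pair. Rejecting H0 needs one favourable component. Confirming H1 needs all of them. The first raises the chance of a false claim of benefit. The second lowers the chance of success below the stated power, and it also asks for a fall in inflammation markers in healthy people. The wording does not choose between the two, so the choice could be made once the results are known.

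**Working it through.** **Inputs**
- Endpoints: 3 (section 4.1). Populations: 2 (section 3.2).
- Alpha 0.05, power 95%, f = 0.2, N = 80, k = 4 groups (section 6.2).
- Measurements m = 4, from the abstract. The text of section 6.2 does not give this number, and its figure is not shown.
- Assumed: correlation between repeated measurements rho = 0.5, sphericity (epsilon = 1), and f = 0.2 for every endpoint.

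**Step 1. Reproduce the plan's figure.** For the within-between interaction, lambda = f²·N·m/(1 − rho), df1 = (k − 1)(m − 1) and df2 = (N − k)(m − 1).
- N = 80: lambda = 0.04 × 80 × 4 / 0.5 = 25.6, df = 9 and 228, power 0.960.
- N = 76: lambda = 24.32, df = 9 and 216, power 0.948.

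So 80 is the smallest multiple of four that reaches 95%, for one endpoint and one test. The required N depends on the assumptions: with m = 4 it is 108 at rho = 0.3 and 48 at rho = 0.7; with rho = 0.5 it is 92 at m = 3 and 112 at m = 2.

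**Step 2. Are H0 and H1 complementary?** Three endpoints in two populations give 2⁶ = 64 patterns of success and failure. H0 as written describes one and H1 one, so 62 satisfy neither. Counting endpoints only, 2³ = 8 patterns, of which 6 satisfy neither.

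**Step 3. If any one favourable result counts as success.** The hypotheses are directional, so a false claim of benefit uses 0.025 per test when tests are two-sided at 0.05.

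| Tests | Favourable direction only, 1 − 0.975ⁿ | Either direction, 1 − 0.95ⁿ |
|---|---|---|
| 1 | 2.5% | 5.0% |
| 3 (independent) | 7.3% | 14.3% |
| 6 (independent) | 14.1% | 26.5% |

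With assumed correlations of 0.3 to 0.7 between endpoints, simulated, the favourable-direction rates are 6.8% to 5.5% for three tests and 13.1% to 10.6% for six. The either-direction rates are 13.6% to 10.9% and 25.3% to 20.7%.

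**Step 4. If all must succeed.** There is no inflation, and each test can be run at 0.05. For three independent endpoints, joint power is 0.95³ = 0.857 on the nominal power, or 0.9595³ = 0.883 on the unrounded power from step 1. Positive correlation between successes would raise it, at most to the single-test value.

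If each population must succeed separately, the comparison is 20 v 20. Then k = 2, N = 40, lambda = 0.04 × 40 × 4 / 0.5 = 12.8, df = 3 and 114, and power is 0.852 per test. It would be 0.782 with m = 3 and 0.693 with m = 2. At 0.852 per test, six independent tests give a joint power of 0.383 (the unrounded 0.85209 to the sixth power).

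**The case against.** **The absence of an alpha procedure.** A reader might infer that the protocol is at fault for having no multiplicity rule outside the microbiome section (6.3). The documents do not support that. Such a rule is commonly left to the SAP, which is not at hand. What stands is narrower: the hypotheses and primary endpoints are stated here, and an SAP could cure their mismatch only by overriding the protocol.

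**The literal 'and' in H1.** If logRSA improves and IL-6 does not, H1 as written is simply not supported, and no error rate is inflated. One might also read H0 loosely as 'not everything improves'. Both are fair. But H0's wording denies each improvement, so one favourable result contradicts it, and the text never says that all components are needed. On this reading the stated power still does not apply.

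**The size.** A reader might take 14.3% and 26.5% as the risk of a false claim of benefit. Those rates count results in either direction, whereas the hypotheses are directional, so 7.3% and 14.1% are the relevant figures. Six tests is also an inference, since the one test named in section 6.2 spans all four groups. Independence is doubtful too, because section 1 describes HRV as associated with CRP and IL-6. Likewise 0.95⁶ = 0.735 might be taken as the joint power for six tests, but it applies the four-group power to per-population comparisons for which it was not calculated.

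**Pilot status.** The protocol calls itself a pilot study in sections 2 and 6.2, so strict familywise control matters less than in a confirmatory trial. This lowers the severity. It does not remove the need for a determinate verdict, because the protocol states formal hypotheses with alpha 0.05 and 95% power.

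**Conclusion.** The point holds as a defect in the stated hypotheses. H0 and H1 leave every mixed result without a verdict, and section 4.1 does not resolve this by ranking the endpoints. This part needs no numerical assumption.

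The size depends on the success rule. If any favourable result suffices, a false claim of benefit has a chance of about 7% (three tests) to 14% (six), against 2.5% for one, assuming independent tests at two-sided 0.05 and somewhat less under positive correlation. If all must succeed, error is controlled but power is about 86–88% for three independent endpoints rather than 95%. It is lower if both populations must succeed separately, with about 85% per test before combining. The 88% and 85% figures rest on four measurements, rho = 0.5 and f = 0.2 for every endpoint.

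The documents do not show that anyone intends to pick the reading afterwards, only that the wording permits it. Severity: should be fixed.

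**What to change.** In section 3.2, rewrite H0 as the exact complement of H1, both as statements about the true probiotic-minus-placebo difference rather than about significant results. State whether that difference is tested in the two populations pooled, in depressed patients only, or in each separately. This matters even with one endpoint: two separate tests with either sufficing give 1 − 0.975² = 4.9% in the favourable direction.

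Then fix one success rule in sections 3.2 and 4.1:
- **Simplest:** logRSA as the single primary endpoint, in line with the aim in section 2, with IL-6 and hs-CRP as key secondary endpoints under Holm. Holm needs no order between the two markers, and the protocol gives no ground for one.
- **Alternative:** keep all three as co-primary, say that all must succeed, and restate the power in section 6.2 for that criterion and the chosen population or populations.

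The cost is a change of protocol wording. Under the first option the inflammation markers can no longer carry the headline claim alone. Under the second, the stated power becomes less favourable.
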